#### Statistical analysis of functional magnetic resonance imaging

In this study, fMRI data will undergo preprocessing using SPM12, including slice-timing correction, head motion correction, spatial normalization to the Montreal Neurological Institute (MNI) space, and spatial smoothing with a 6-mm Gaussian kernel. Functional brain networks will be constructed using both seed-based functional connectivity and ICA. For seed-based connectivity, regions of interest (ROIs) will be defined using the Automated Anatomical Labeling (AAL) atlas, and the mean BOLD signal from each ROI will be correlated to generate a connectivity matrix. Group ICA will be conducted using the GIFT software, decomposing the BOLD data into spatially independent components (ICs) that will be matched to canonical brain networks such as the default mode network (DMN), salience network (SN), and frontoparietal network (FPN). Additionally, graph-theoretical metrics, including degree centrality, clustering coefficient, and small-worldness, will be calculated to assess network efficiency and integration. Statistical analyses will involve comparing connectivity strength, network properties, and regional activations between groups using paired or independent t-tests, with corrections for multiple comparisons. Correlations between connectivity measures and clinical outcomes, such as HAMD scores, will be examined using Pearson or Spearman correlation coefficients. This comprehensive approach ensures robust exploration of functional brain networks and their clinical relevance.

#### Statistical analysis of near infrared brain functional imaging

To evaluate statistical differences between the two groups, *t*-tests are conducted using MATLAB 2017 (MathWorks). Specifically, independent sample *t*-tests are performed to compare the mean activation levels between the two groups, while paired *t*-tests are used to assess activation changes within the PSD group before and after treatment. All data are presented as mean ± SD. Additionally, to validate the results of functional connectivity analyses, both independent sample and paired *t*-tests are applied.

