**Methods and analysis:**

This study is a non-inferiority randomized controlled trial (RCT). One hundred and twenty-eight participants with PSD will be randomly assigned (1:1) to the intervention group (Tuina + rTMS treatment) and the control group (cognitive behavior treatment). The primary efficacy outcome is the change from baseline to week 2 in Hamilton Depression Rating Scale (HAMD) and Functional Magnetic Resonance Imaging (fMRI). Secondary efficacy outcomes include other assessments of the Mini-Mental State Examination (MMSE), The modified Barthel index (MBI), The National Institutes of Health Stroke Scale(NIHSS), inflammatory factor (IL-6, IL – 17, TNF-*α*, IFN-*γ*, IL-4, IL-10), and Functional near-infrared spectroscopy (fNIRS). Efficacy and scale assessments will be conducted at 1 month and 3 months after the completion of treatment.

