#### Secondary outcomes

The Mini-Mental State Examination (MMSE) is widely used to assess the cognitive function in various clinical conditions, including post-stroke depression. This 30-point questionnaire evaluates domains such as orientation, attention, memory, language, and visuospatial abilities. A higher score indicates better cognitive function. In this study, MMSE will be used to evaluate cognitive status at baseline and after 12 weeks of intervention.

The modified Barthel index (MBI) is employed to evaluate the level of functional independence in activities of daily living (ADLs). The scale comprises 10 items, including feeding, bathing, grooming, dressing, and mobility. The scores range from 0 to 100, with higher scores reflecting greater independence. As PSD may negatively impact recovery in ADLs, the MBI serves as an essential secondary indicator of functional improvement.

The National Institutes of Health Stroke Scale (NIHSS) is a standardized tool used to quantify neurological deficits in stroke patients. It assesses multiple domains, including consciousness, motor strength, sensation, language, and visual fields. Scores range from 0 to 42, with higher scores indicating more severe deficits. Monitoring NIHSS scores provides insight into the interplay between PSD and the neurological recovery process.

Functional near-infrared spectroscopy (fNIRS) is conducted using two wavelengths of near-infrared light (690 nm and 830 nm) to measure oxygenated hemoglobin (oxy-Hb) based on the modified Beer–Lambert law. FNIRS assessments is performed at baseline, after 1 and 2 weeks of treatment. The study employed the Verbal Fluency Task (VFT) as a cognitive task to activate brain regions during fNIRS measurements, which is conducted on the same day as the tasks.

In this study, we selected IL-6, IL-4, IL-10, IL-17, TNF-*α*, interferon-*γ* (IFN-γ), adrenocorticotropic hormone (ACTH), and cortisol as key biomarkers to evaluate the interplay between inflammatory processes and hypothalamic–pituitary–adrenal (HPA) axis function in PSD. Pro-inflammatory cytokines such as IL-6, IL-17, TNF-α, and IFN-γ were measured to assess the level of systemic inflammation, which has been implicated in the pathophysiology of PSD. Anti-inflammatory cytokines, including IL-4 and IL-10, is evaluated to explore their potential regulatory effects. Additionally, ACTH and cortisol levels is used as indicators of HPA axis activation and stress response.

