### Statistical analysis

#### Statistical analysis of scales and general information

All statistical analyses will be performed using SPSS version 26.0. Continuous variables will be presented as mean ± standard deviation (SD) and compared using independent t-tests or Mann–Whitney U tests based on data normality. Categorical variables will be expressed as frequencies and percentages and analyzed using chi-square or Fisher’s exact tests. Missing data will be handled using multiple imputation. To control for potential confounders, a multivariate regression analysis will be conducted. A two-tailed *p*-value < 0.05 will be considered statistically significant.

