#### Statistical analysis of functional magnetic resonance imaging

Image data analysis is performed using Network Based Statistics (NBS) V1.2 statistical software based on MATLAB platform to construct local brain functional networks for two groups of subjects. Brain network features within each group are constructed through single sample *t*-test. The network between the observation group and the control group before and after treatment is compared using a two independent sample *t*-test; Multiple comparisons between local brain functional networks are corrected for false discovery rate (FDR). The difference is considered statistically significant with *p* < 0.05. The results of brain function data are presented using BrainNet Viewer 1.6 software. The significant brain regions detected before and after treatment are compared between the control group and the observation group. SPSS 25.0 software is used to perform correlation analysis with clinical scale scores. Pearson correlation is selected for normal distribution, while Spearman correlation is selected for non-normally distributed data. *p* < 0.05 is considered statistically significant. The results of the relevant analysis data are presented using the statistical parameter graph software Origin 2021.

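### The fNIRS section prescribes plain t-tests for activation and connectivity and states no multiplicity correction, unlike the fMRI sections on either side of it

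*Protocol article*

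**What the plan says.** The section on statistical analysis of near infrared brain functional imaging is devoted to fNIRS and names the software and the tests. Between arms, "independent sample *t*-tests are performed to compare the mean activation levels between the two groups". Paired t-tests "are used to assess activation changes within the PSD group before and after treatment". For connectivity, "to validate the results of functional connectivity analyses, both independent sample and paired *t*-tests are applied". The section gives no correction, no list of channels or regions, and no significance threshold. The threshold stated with the general analysis methods, under scales and general information, is "A two-tailed *p*-value < 0.05 will be considered statistically significant".

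The two neighbouring sections, which share one fMRI heading, both mention correction. The first compares groups "using paired or independent t-tests, with corrections for multiple comparisons". The second says "Multiple comparisons between local brain functional networks are corrected for false discovery rate (FDR").

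On timing, the Secondary outcomes section says "FNIRS assessments is performed at baseline, after 1 and 2 weeks of treatment", whereas Table 1 marks fNIRS only at weeks 0 and 2.

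**The concern.** The article states multiplicity control for imaging twice, and the fNIRS section between those two statements has none. An analyst who followed it literally would run uncorrected tests on activation and on connectivity.

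The end of the Introduction relies on fMRI and fNIRS together to show remodelling of neural networks. A chance difference in one channel or one connection could therefore be reported as evidence of how Tuina plus rTMS works, on a looser standard than the fMRI results reported beside it.

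**Working it through.** **The plan's own figure.** The only computed figure in the article is the HAMD sample size: (1.96 + 0.84)² × 2 × 4.49² / 2.5² = 50.58, so 51 per group; 51 / 0.8 = 63.75, so 64 per group and 128 in total. This reproduces. It does not bear on the fNIRS question, except that about 51 evaluable patients per arm is the natural size for a simulation.

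**Inputs.**
- Per-test level: 0.05 two-sided, taken from the scales section because the fNIRS section states none.
- Between-arm endpoints: at least two, activation and connectivity (fNIRS section).
- Post-baseline visits: one (Table 1) or two (Secondary outcomes).
- Number of channels and their correlation: not given. Assumed 16, 22 or 48 channels, with a common correlation between 0 and 0.8.

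**Smallest families, independent tests.** The chance of at least one false positive among m tests is 1 − 0.95^m.
- One averaged activation value at one visit: 5.0%.
- One activation and one connectivity value at one visit: 1 − 0.95² = 9.8%. With correlation 0.8 between the two tests, simulation gives about 8%.
- The same two values at two visits: 1 − 0.95⁴ = 18.5%.

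**Channel-wise activation, one visit.** The correlation 0 column is the formula. The others are simulations with no true effect and equally correlated test statistics.

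| Channels | Correlation 0 | 0.3 | 0.5 | 0.8 |
|---|---|---|---|---|
| 16 | 56% | 48% | 38% | 21% |
| 22 | 68% | 56% | 44% | 23% |
| 48 | 91% | 80% | 61% | 29% |

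Simulations with t-tests on 51 patients per arm agree to within about two percentage points. At correlation 0.9, the figures for 10 to 52 tests are 13% to 20%.

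**Connectivity.** If every pair of channels is tested, the count is k(k − 1)/2: 16 × 15 / 2 = 120 pairs, or 22 × 21 / 2 = 231. At 0.05 each, the expected number of false pairs is 120 × 0.05 = 6 or 231 × 0.05 = 11.6, whatever the correlation. The chance of at least one depends heavily on the correlation. It was about 30% in a simulation where one global signal dominated, and is near 100% if pairs are independent.

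**After the fix.** In the same channel-wise simulations, Benjamini-Hochberg at q = 0.05 over one family kept the chance of any false claim at about 5% or below throughout. When no effect exists anywhere, every rejection is false, so the false discovery rate and the familywise rate coincide. If activation and connectivity are corrected as two separate families, the overall chance can reach 1 − 0.95² = 9.8%.

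**The case against.** The strongest reply is that silence is not a decision. The article does not say that fNIRS results will be left uncorrected, and channel layout and multiplicity for a secondary mechanistic outcome are often settled in an analysis plan, which is not shown here. That stands as far as intent goes. It does not remove the inconsistency within the article, which gives multiplicity control at this level of detail for fMRI and omits it in the one section written for fNIRS.

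A reader might infer that a significant fNIRS difference would often appear by chance. The documents do not support that. The number of tests and their correlation are not stated, and the activation comparison might be a single averaged value per patient. The Discussion's remark about specific cortical regions describes what fNIRS can do in general, not what this trial will test. The article also does not say that any one positive channel will be read as a treatment effect.

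Week 1 is another weak support for a large figure, since Table 1 does not list fNIRS at that visit.

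Finally, the second fMRI section follows directly after the fNIRS section and speaks broadly of brain function data, so its FDR step might be meant to reach fNIRS networks. Even on that reading it concerns networks and would leave the activation tests without a stated correction.

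**Conclusion.** The point holds as an inconsistency with a concrete remedy, on a secondary outcome. Run as written, the between-arm fNIRS comparisons carry more than a 5% chance of at least one false difference as soon as more than one channel, region, pair or visit is tested, and activation plus connectivity already makes two tests. How far above 5% cannot be read from the article. The two-test figure of about 10% assumes independence, and the range of roughly 20% to 90% rests entirely on the assumed 16 to 48 channels and correlations from 0.8 to 0. The claim goes no further than this: a correction is not stated, rather than ruled out. The HAMD conclusion and the sample size are untouched.

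**What to change.** In the fNIRS analysis section, apply the FDR control already stated for the fMRI networks. Suggested text: *Between-arm fNIRS comparisons will be corrected by the Benjamini-Hochberg procedure at q < 0.05 across all channels or regions and all connectivity pairs at the post-baseline visits analysed. Uncorrected results will be labelled exploratory.* Treat activation and connectivity as one family or, if they are kept apart, state that the error rate is per family.

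To define the family, name the channels or regions tested, and reconcile the fNIRS visits in Secondary outcomes (weeks 1 and 2 after baseline) with Table 1 (week 2 only). Also say whether the FDR sentence in the second fMRI section is meant to cover fNIRS networks.

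The cost is a few sentences and a line of analysis code, with no new data. The downside is lower sensitivity for any single channel or connection.

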#### Statistical analysis of functional magnetic resonance imaging

Image data analysis is performed using Network Based Statistics (NBS) V1.2 statistical software based on MATLAB platform to construct local brain functional networks for two groups of subjects. Brain network features within each group are constructed through single sample *t*-test. The network between the observation group and the control group before and after treatment is compared using a two independent sample *t*-test; Multiple comparisons between local brain functional networks are corrected for false discovery rate (FDR). The difference is considered statistically significant with *p* < 0.05. The results of brain function data are presented using BrainNet Viewer 1.6 software. The significant brain regions detected before and after treatment are compared between the control group and the observation group. SPSS 25.0 software is used to perform correlation analysis with clinical scale scores. Pearson correlation is selected for normal distribution, while Spearman correlation is selected for non-normally distributed data. *p* < 0.05 is considered statistically significant. The results of the relevant analysis data are presented using the statistical parameter graph software Origin 2021.

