#### Primary outcomes

The primary outcome measure for evaluating the severity of post-stroke depression is the 17-item Hamilton Depression Rating Scale (HAMD-17). This scale is a clinician-administered tool that quantitatively assesses depressive symptoms across multiple domains, including mood, anxiety, physical complaints, and psychomotor changes. HAMD-17 is particularly suitable for PSD as it captures somatic symptoms often present in stroke patients. A score >7 and ≤ 24 will be used to confirm mild to moderate depression, ensuring appropriate inclusion of participants in the study. Assessments will be conducted at baseline, midpoint (1 weeks), and at the end of the intervention (2 weeks) to evaluate changes in depressive symptoms over time. All evaluations will be performed by trained and blinded assessors to minimize measurement bias and maintain the integrity of the study.

In this study, rs-fMRI will serve as the second primary outcome measure to investigate neural mechanisms underlying post-stroke depression and its treatment effects. The imaging data were acquired using a United Imaging uMR780 3.0 T MRI system equipped with a 32-channel rigid head coil. Participants wore noise-canceling headphones, kept their eyes closed, remained awake, and minimized thoughts. The T1-weighted (T1W1) structural imaging parameters were as follows: TR = 7.2 ms, TE = 3.1 ms, flip angle = 10°, field of view (FOV) = 256 mm × 256 mm, slice thickness = 1 mm, and 192 slices. fMRI parameters included: TR = 2000 ms, TE = 30 ms, flip angle = 90°, FOV = 224 mm × 224 mm, matrix size = 64 × 64, and 33 slices. The voxel size was 3.5 mm × 3.5 mm × 3.5 mm, with 240 time points collected in each scan session, lasting 8 min per session.

Resting-state fMRI data were preprocessed using SPM12 software. The preprocessing steps included slice timing correction to account for temporal offsets in slice acquisition, realignment to correct for head motion, and coregistration of the functional images to the corresponding T1-weighted structural images. Segmentation of the T1 images was performed to generate normalization parameters, which were applied to transform the functional images into MNI space. Finally, spatial smoothing was conducted using a 6-mm FWHM Gaussian kernel to enhance the signal-to-noise ratio.

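### fMRI is a primary outcome defined as change, but the imaging sections name no between-arm test that uses each patient's baseline scan

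*Protocol article*

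**What the plan says.** The abstract of the protocol article (Methods and analysis) states: "The primary efficacy outcome is the change from baseline to week 2", and attaches this to both HAMD and fMRI. The Primary outcomes section confirms the status of imaging: "rs-fMRI will serve as the second primary outcome measure to investigate neural mechanisms underlying post-stroke depression and its treatment effects". fNIRS is a secondary outcome, and the abstract does not define it as change.

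Three sections then describe the imaging tests.

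- **First fMRI analysis section:** it compares connectivity strength, network properties and "regional activations between groups using paired or independent t-tests, with corrections for multiple comparisons".
- **fNIRS analysis section:** change is examined by paired testing only; such tests "are used to assess activation changes within the PSD group before and after treatment". The contrast of arms is on the level of activation: unpaired tests "are performed to compare the mean activation levels between the two groups".
- **Second fMRI analysis section** (same title as the first): within-group network features come from one-sample t-tests. Then "The network between the observation group and the control group before and after treatment is compared using a two independent sample" t-test, with FDR correction. Regions that reached significance before and after treatment are afterwards compared across the two arms.

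A multivariate regression for confounders is planned, but it stands in the section on scales and general information, not in the imaging sections.

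**The concern.** The declared estimand for a primary outcome is a difference between arms in change. The named tests do other things: they compare arms at one time, test change inside one group, or compare lists of significant findings. Three problems follow.

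1. A between-arm test before treatment says nothing about the treatment. With sound randomisation, any difference there is chance.
2. Finding significance in one arm or at one time, and not in the other, does not show that the arms differ. Comparing separately thresholded regions invites exactly that conclusion.
3. The fNIRS change test does not say whose change it is. Every participant has PSD, so the wording could pool the arms or cover only one of them.

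At stake is how the mechanistic claim will be supported. Several unranked tests are on offer for a primary outcome. The one that is valid for the arm effect ignores a baseline scan that Table 1 already schedules.

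**Working it through.** **The plan's own figure.** The sample size section gives Δ = 2.5 and σ = 4.49 (HAMD), two-sided 5%, 80% power:

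n = (1.96 + 0.84)² × 2 × 4.49² / 2.5² = 7.84 × 40.32 / 6.25 = 50.58, so 51 per arm. With 20% dropout, 51 / 0.8 = 63.75, so 64 per arm and 128 in total.

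This reproduces. The point is therefore about the contrast tested, not the number of patients. No effect size, SD or pre-post correlation is given for imaging, so those below are assumptions.

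**How often two within-arm tests disagree when the arms do not differ.** Take n = 51 per arm, the same true change d in both arms (in SDs of the measure), and pre-post correlation ρ. The SD of a change score is √(2(1−ρ)), so the paired t-test has 50 degrees of freedom and noncentrality d√51 / √(2(1−ρ)). With power p in each arm, the chance that exactly one arm is significant is 2p(1−p).

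Example: d = 0.3, ρ = 0.5. Noncentrality = 0.3 × 7.141 / 1 = 2.14, p = 0.556, and 2 × 0.556 × 0.444 = 0.494.

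| ρ | d = 0.2 | d = 0.3 | d = 0.4 | d = 0.5 |
|---|---|---|---|---|
| 0.3 | 34% | 49% | 45% | 27% |
| 0.5 | 41% | 49% | 32% | 12% |
| 0.7 | 49% | 35% | 9% | 1% |

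If neither arm changes, the figure is 2 × 0.05 × 0.95 = 9.5%. A direct test of the arm difference would be falsely positive 5% of the time throughout, per test and before multiplicity correction.

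**What the baseline scan is worth.** The variance of the estimated arm difference, relative to a week-2-only comparison (= 1), is 2(1−ρ) for change scores and 1−ρ² for the baseline-adjusted week-2 value (large-sample form).

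- ρ = 0.4: 1 − 0.16 = 0.84, a 16% cut for the adjusted analysis.
- ρ = 0.6: 1 − 0.36 = 0.64, a 36% cut.

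In power terms, borrow the HAMD standardised effect, 2.5 / 4.49 = 0.557 SD, for lack of an imaging one, at 51 per arm:

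| ρ | Week-2 only | Change score | Baseline-adjusted |
|---|---|---|---|
| 0.3 | 80% | 66% | 84% |
| 0.5 | 80% | 80% | 90% |
| 0.7 | 80% | 95% | 98% |

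The baseline-adjusted test is best in every row. The change score is worse than week-2 only when ρ is below 0.5.

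**The case against.** A reader might infer that the question of whether Tuina plus rTMS alters networks more than CBT is never tested. The article does not support that. Allocation is randomised 1:1, so the expected week-2 difference equals the expected difference in change. The post-treatment two-sample t-test is therefore an unbiased test of the arm effect. This stands, and it reduces that part of the point to lost precision.

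Other defences carry some weight.

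- **Within-arm tests may be meant as descriptive.** The one-sample tests read that way, and the fNIRS section also has a direct between-group test. Nowhere does the article say that significance in one arm only will count as proof. But the second fMRI section does carry significant regions forward into a comparison between arms, and nothing is labelled descriptive.
- **Paired or independent in the first fMRI section** most naturally means paired for before and after, and independent for the arms. It need not mean that independent patients will be paired. That stronger charge is not made here.
- **The second fMRI section could mean a t-test on change.** It speaks of comparing the network and mentions no difference score. A primary analysis open to two readings still needs fixing.
- **A condensed article leaves detail to an SAP.** True, and for that reason the absence of a multiplicity correction for fNIRS is not pressed: the fMRI sections state one, but this may be left to the SAP. The contrast itself is different, because the article names the tests, and those named do not match the outcome.
- **The change definition does not cover fNIRS.** Correct. For fNIRS the fault rests only on the analysis section assessing change in an unidentified group.

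**Conclusion.** The point holds in limited form. For a primary outcome defined as change, no between-arm test using the baseline scan is named. The valid test that is named, at week 2, is unadjusted and sits beside two comparisons that carry no evidence of a treatment difference: arms before treatment, and separately significant regions. The fNIRS change test does not identify an arm.

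The lost precision is a 16% to 36% larger variance reduction forgone at a correlation of 0.4 to 0.6. The risk from reading within-arm results as a contrast is a discordance of 1% to 49% with no true difference, for changes of 0.2 to 0.5 SD and correlations of 0.3 to 0.7. That range is wide because the article gives no imaging SD, effect or correlation. It also assumes usable scans from 51 patients per arm. It describes a misuse that the plan leaves open, not one that it commits itself to.

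**What to change.** In all three imaging analysis sections:

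1. Name one efficacy test for each fMRI and fNIRS measure: the arm effect on the week-2 value, with the patient's baseline value of the same measure as covariate. Enter it as an ANCOVA design in NBS or SPM and in the fNIRS model. The baseline value differs by connection, voxel or channel, so check that the software accepts such a covariate. If it does not, fit the model outside it or name a fallback in advance. Change scores would serve, at a cost in power if the correlation is below 0.5.
2. Drop the pre-treatment between-arm test and the comparison of separately significant regions as evidence of effect. Report baseline imaging by arm descriptively.
3. Label the one-sample and paired tests as descriptive, and replace the reference to a PSD group with the named arm or arms.
4. State that week 2 is the fNIRS time point for the efficacy test. The Secondary outcomes section says "FNIRS assessments is performed at baseline, after 1 and 2 weeks of treatment", while Table 1 shows only weeks 0 and 2.

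The cost is revised wording and a different design matrix. No extra scans, patients or visits are needed. The change should be made before any imaging data are compared by arm.

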### Sample size calculation

The sample size for this study was calculated based on data from a previous clinical trial (20), in which the HAMD score was 9.90 ± 4.61 in the Tuina therapy group and 13.24 ± 4.36 in the conventional rehabilitation group. The combined standard deviation (*σ*) was 4.49. To detect a difference between group means (*Δ* = 2.5) with a statistical power of 80% (*β* = 0.2, corresponding to Zβ = 0.84) and a significance level of 0.05 (*α* = 0.05, corresponding to Zα/2 = 1.96), the required sample size per group was calculated using the following formula, with calculations performed in G*Power software to ensure adequate statistical power:

$$n=\frac{{\left(Z_{\alpha /2}+Z_{\beta }\right)}^{2}\cdot 2\sigma^{2}}{\Delta^{2}}$$

Thus, each group requires approximately 51 participants. Considering a 20% dropout rate, the adjusted sample size is 64. Therefore, a total of 64 participants per group will be required, resulting in a total sample size of 128 participants.

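### The last step of the fMRI analysis compares "significant" regions between arms without saying which contrast selects them; if within-arm significance in the same scans does, the p-values and any FDR within that set are invalid

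*Protocol article*

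**What the plan says.** The protocol article has two sections headed Statistical analysis of functional magnetic resonance imaging. The second sets out a sequence:

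1. "Brain network features within each group are constructed through single sample" *t*-test.
2. "The network between the observation group and the control group before and after treatment is compared using a two independent sample" *t*-test.
3. "Multiple comparisons between local brain functional networks are corrected for false discovery rate (FDR", with significance declared at p < 0.05.
4. After a sentence on display software: "The significant brain regions detected before and after treatment are compared between the control group and the observation group".

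Correlations with the clinical scales follow.

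The first section with that heading takes a different route: "regions of interest (ROIs) will be defined using the Automated Anatomical Labeling (AAL) atlas", and groups are compared "with corrections for multiple comparisons". Under Primary outcomes, "rs-fMRI will serve as the second primary outcome measure".

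**The concern.** The regions in step 4 enter because they are already significant in these scans. The text does not say whether that means significant within an arm (single-sample or pre-post) or between arms. It mentions no hold-out data and no pooled, arm-blind mask. FDR is attached to the network comparison in step 3, not to step 4.

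Selection within an arm is the harmful case. A chance high value in one arm puts a region on the list, and the same chance value pushes the two arms apart. Given selection, the p-value of a null region is then no longer uniform, and FDR applied to such p-values does not control what it claims to control.

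At stake is the reliability of a list of regions reported as differing between arms on a primary outcome, and the size of the differences reported for them.

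**Working it through.** **The plan's own figure.** The article gives no error rate or sample size for fMRI. Its only computed figure is the HAMD-17 sample size, with 80% power (Zβ = 0.84), two-sided 5% ("corresponding to Zα/2 = 1.96"), σ = 4.49 and Δ = 2.5:

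n = (1.96 + 0.84)² × 2 × 4.49² / 2.5² = 7.84 × 40.32 / 6.25 = 50.6, so 51 per arm; 51 / 0.8 = 63.75, so 64.

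This reproduces. I use 51 evaluable per arm below.

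**Assumptions, because the article gives none of these.** Normal data; independent arms; no true arm difference; a region is selected if it is significant in at least one arm; selection thresholds 0.05, 0.01 and 0.001; between-arm *t*-test at two-sided 0.05.

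**Error among selected regions (simulation).**

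| True within-arm standardised mean, equal in both arms | selected at 0.05 | at 0.01 | at 0.001 |
|---|---|---|---|
| 0 | 33% | 53% | 76% |
| 0.2 | 9.5% | 17% | 32% |
| 1.0 | 5% | 5% | 5% |

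A large-sample normal version gives 33% and 77% for the first row at 0.05 and 0.001. Selecting on the pooled sample gives 5.0%, because the pooled mean is independent of the arm contrast.

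**Unconditional rate per null region.** P(selected) = 1 − (1 − α)². With no within-arm signal:

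- 0.05: 1 − 0.95² = 0.0975; × 0.33 = 3.2%
- 0.01: 1 − 0.99² = 0.0199; × 0.53 = 1.1%
- 0.001: 1 − 0.999² = 0.0020; × 0.76 = 0.15%

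The general bound is simple: a region declared different must be selected and have p < 0.05, and the second event alone has probability 5%.

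**FDR run only inside the selected set.** Depending on within-arm signal and selection threshold, the chance of at least one false arm difference is 6% to 99%, against about 5% when FDR is run on the full set. The top of that range needs many weak, independent units, for example edges (90 regions, an assumed count, give 90 × 89 / 2 = 4,005).

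**Selection by the between-arm test itself.** Re-testing the same contrast returns the same regions, so it adds no error and no information. The estimates are inflated: at 51 per arm a difference reaches p < 0.05 only if it exceeds about 1.98 × √(2/51) = 0.39 SD. A true difference of 0.3 SD is therefore reported as about 0.52 on average among the regions that pass (uncorrected 0.05).

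**Selection on a follow-up difference, then a test of change.** These are different but correlated contrasts. The conditional error is 13% to 24% with selection at 0.05 and 27% to 55% at 0.001 (baseline/follow-up correlation 0.7 to 0.3).

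**The case against.** The strongest reply is that the sentence may be no more than reporting. It names no test, threshold or p-value, it follows the FDR-corrected two-sample comparison, and it may simply refer to the regions that comparison found. Nothing restricts the two-sample network test to edges that passed the single-sample tests. The first fMRI section, with atlas regions and a multiplicity correction, already contains most of a valid analysis: FDR over all pre-defined regions gave a 5.0% to 5.4% chance of any false difference (90 or 116 independent regions assumed). One-sample tests of connectivity also tend to pick up edges with real signal in both arms, where selection does no harm. A condensed article may leave the mask and threshold to the full protocol.

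Much of this stands. A reader might infer that null regions will be declared different far more often than 5% of the time. The documents do not support that: the high figures are conditional on selection, and no selection step can lift the unconditional rate of a null region above 5%. Nor do they support calling the whole fMRI analysis circular.

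What does not fall is narrower. The text says the regions are compared, gives this as a step separate from the FDR-corrected test, and states no correction for it. Nothing says which of the two fMRI sections governs. A valid route elsewhere in the article does not make p-values from this step valid.

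**Conclusion.** The point holds conditionally. The article states a between-arm comparison of regions already found significant, on a primary outcome, and leaves open the contrast that defines significance.

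- Selected by within-arm significance in the same scans: the p-values and any FDR within the set are invalid. The error among selected regions is 5% where signal is strong in both arms and 33% to about 77% where there is none.
- Selected by the FDR-corrected between-arm test and re-tested on the same contrast: no added false positives, but redundant, with overstated effects.
- Description only: no inferential harm, provided no p-values are attached.

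The upper figures are the no-signal case and not a forecast for this trial. They rest on assumed thresholds, normal data and an either-arm selection rule. Independence between regions or edges matters only for the any-false-difference figures.

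**What to change.** State that the only inferential between-arm fMRI comparison is a single two-sample test with FDR over one common set of regions or edges. Fix that set without using arm or within-arm significance: all the AAL regions or edges named in the first fMRI section, or a mask built from pooled, arm-blind scans. Use the single-sample maps, and the values from the regions called significant, for description only and without p-values, noting that estimates from selected regions are exaggerated. Say that this rule governs both fMRI sections.

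The cost is a change of wording, with no new data. FDR over the full set is somewhat more conservative than over a preselected one.
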